We structured a Monte Carlo power analysis for Objectives 1 and 2 by structuring a population model reflecting weekly assessments for a 3-month lead-in period, a 12-month active intervention phase, and a 6-month sustainment period. The mean and standard deviation of the number of people who test for HIV in the target SSPs was 7.32 (2.94); these values were used as the run-in period mean and SD in the simulation. Effect sizes from a pilot study that used a similar SAIA platform ranged from.48 to 1.50; thus, we power the current study in anticipation of large effect sizes (d = .8). The mean shift in post-implementation outcomes favoring SAIA that corresponds to an effect size of.8 would be an additional 2.35 people tested under SAIA. The per-week increase in number tested under SAIA to reach a longitudinal Cohen’s d effect size of.8 by 11 weeks would be an increase of.21 persons per week. We generated 250 synthetic samples of n = 32 and analyzed the samples in Mplus while imposing (a) the random effect structure from pilot estimates and (b) a state-level ICC of.05. Power to detect a post-implementation mean shift and differences in slopes over time were greater than 80%. Detecting treatment effect deterioration from months 1–12 to month 13–18 for power of.80 requires deterioration equivalent to a Cohen’s d of.48; despite a sample size of 32, the extremely large number of repeated measures offsets the sample size with regard to statistical power to detect slope differences.

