Despite these limitations, the SAIA-SSP-HIV trial, to our knowledge, represents the first RCT of an implementation strategy focused on improving an infectious disease care cascade within SSPs. It builds upon a prior pilot study suggesting the potential effectiveness of SAIA for increasing naloxone distribution through two SSPs, which resulted in a 105% average increase in the number of doses of naloxone distributed per week following initiation of the SAIA implementation strategy [28]. However, delivering HIV services in non-clinical settings like SSPs involves a distinct care cascade conceptualization, warranting additional testing through a sufficiently powered implementation trial to detect effectiveness of SAIA-SSP-HIV. Additionally, because SSPs’ operational structures vary substantially across U.S. states and local jurisdictions, this study also seeks to expand the translatability of SAIA by exploring implementation outcomes among diverse SSPs located across the country.

In conclusion, SAIA-SSP-HIV could help optimize the delivery of HIV testing and referrals in community settings that are frequented by a vulnerable, at-risk population. As the first implementation trial focused on an infectious disease care cascade within SSPs, findings from the SAIA-SSP-HIV trial will shed light on how to support non-clinical settings in optimizing delivery of screening services and subsequent referrals into clinical care. If effective, SAIA-SSP-HIV could potentially be scaled up in support of key Ending the HIV Epidemic initiatives [8,51] and could possibly be adapted for optimizing other care cascades in SSPs and other community settings.

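### The slope used for power reaches d = 0.8 at 11 weeks, which does not fit a linear 12-month phase: either the slope power is for d of about 3.7 at month 12, or the per-week unit is wrong

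*Protocol article*

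**What the plan says.** All the power figures are in the Protocol article, section 'Analyses and power calculations'. The population model is described as "reflecting weekly assessments for a 3-month lead-in period, a 12-month active intervention phase", followed by a 6-month sustainment period. The run-in mean is 7.32 people tested, with SD 2.94. On effect size: "Effect sizes from a pilot study that used a similar SAIA platform ranged from.48 to 1.50", and so "we power the current study in anticipation of large effect sizes (d = .8").

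That target is then expressed in two ways. As a mean shift, it "would be an additional 2.35 people tested under SAIA". As a slope, the weekly gain that attains d = 0.8 "by 11 weeks would be an increase of.21 persons per week". Power is reported as above 80% for both the mean shift and the slope difference, from 250 simulated samples of 32 programs with a random-effect structure taken from pilot estimates whose values are not printed. The paragraph ends by arguing that "the extremely large number of repeated measures offsets the sample size with regard to statistical power to detect slope differences".

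Earlier in the same section the assumed time course is piecewise linear, with phases for the lead-in, the period after implementation starts, and a deterioration phase between months 12 and 18. Non-linear forms are mentioned only as a possibility. The model has random slopes by program. The first objective places its hypothesis over the 12-month implementation period.

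**The concern.** The 11-week horizon is unexplained and matches no phase of the design: the lead-in is 3 months, implementation 12 and sustainment 6. If a linear slope is set to reach the target effect at week 11 and the phase runs about 52 weeks, the effect keeps growing for the other 41. The slope test is then powered for something far larger than d = 0.8 at the end of implementation.

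The slope is not a side issue, because the model section identifies the arm difference after implementation partly through the interaction of arm with time. If the quoted slope power belongs to a much steeper slope, a null slope result could be read as coming from a test adequately powered for d = 0.8 at month 12 when that has not been shown.

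**Working it through.** **Inputs.** From 'Analyses and power calculations': SD 2.94, mean 7.32, d = 0.8, slope 0.21 per week, 11 weeks, pilot range 0.48 to 1.50, weekly data over 12 months (taken as 52 weeks). From 'Study design': 16 programs per arm.

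**Reproducing the plan's figures.**
- Mean shift = d × SD = 0.8 × 2.94 = 2.352 (stated 2.35).
- Slope = 2.352/11 = 0.214 per week (stated .21).

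**Carrying the slope through the phase.** Implied d at week T = 0.21 × T/2.94.

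| Week | Extra people tested per week | Implied d |
|---|---|---|
| 11 | 2.31 | 0.79 |
| 21 | 4.41 | 1.50 (top of the pilot range) |
| 26 | 5.46 | 1.86 |
| 52 | 10.92 | 3.71 |

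At week 52 the gain is 10.92/7.32 = 149% of the run-in mean. Relative to the target, 3.71/0.8 = 4.6.

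**Slope that gives d = 0.8 at week 52.** 2.352/52 = 0.045 per week.

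**Monthly reading.** Twelve monthly points have 11 steps. If 0.21 were per month, the weekly equivalent is 0.21 × 12/52 = 0.048, close to 0.045. On this reading the effect size fits the 12-month phase and only the unit is wrong.

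**Power at 0.045 per week.** The stated power cannot be reproduced, because the random-effect variances, alpha and sidedness are not printed. As an approximation, take a least-squares slope for each program and compare arms with a two-sample noncentral t test on 30 df:
- slope SD per program = √(τ² + σ²/Sxx)
- Sxx = 52 × (52² − 1)/12 = 11,713
- σ² = (1 − ICC) × 2.94²

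Here τ is the between-program SD of true slopes. Assumed, not in the article: two-sided alpha 0.05, ICC 0.2 to 0.5, and each τ below.

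| τ (per week) | Power at 0.045 per week | Same, ten times the measurements |
|---|---|---|
| 0.02 | 98–99% | above 99% |
| 0.03 | 89–94% | 98% |
| 0.04 | 75–80% | 86% |
| 0.045 | 68–72% | 77–78% |
| 0.07 | 39–40% | 42% |

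At 0.21 per week, power is close to 100% for every τ in the table and still about 81% at τ = 0.20, where 0.045 per week has about 9%. A figure above 80% at 0.21 per week therefore says little about power at 0.045 per week.

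**The 'offsets' argument.** More weeks enlarge Sxx and shrink σ²/Sxx, but they leave τ² unchanged. The last column shows the result: extra measurements help when τ is small and do little when τ is large.

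**The case against.** The strongest reply has several parts.

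*The same power sentence covers a mean shift set correctly at d = 0.8.* This stands. The defect is confined to the slope statement, and a reader who inferred that the trial's whole power claim fails would be going beyond the document.

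*The value d = 3.7 needs a straight line to week 52, and the article does not print the simulated trajectory after week 11.* This stands as a condition. But linear change is the article's stated assumption, non-linear forms are only a contingency, and no plateau or break at week 11 appears anywhere.

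*The article never says d = 0.8 at month 12 for the slope.* True: its only slope horizon is 11 weeks. Yet it names d = 0.8 as the effect the study is powered for and sets the hypothesis over 12 months, so the horizon has to be reconciled with both.

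*If the 11 steps are months, the power may be for the right effect.* This stands too, and is why the conclusion is an either/or.

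A reader might also infer that true slope power is below 80%. The document does not support that: with a slope SD of 0.03 per week or less, power at 0.045 per week stays at about 89% or higher, and the SD is not reported. Nor can it be said that the random-effect values came from the pilot described in the Discussion as "increasing naloxone distribution through two SSPs", because the power paragraph does not identify its source. No error is shown in the deterioration figure (d of .48), and the absence of referral inputs from a condensed article does not show that referrals were left out of the simulation.

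**Conclusion.** The slope sentence is wrong as written. On the article's own figures and its assumed linear form, 0.21 per week means d of about 3.7 at week 52, some 4.6 times the stated target and well above the largest pilot effect. The alternative is that 0.21 is a monthly step and the per-week label is mistaken. On the first reading, the slope part of the above-80% claim is not power for d = 0.8 over the 12-month phase. On the second, only the unit needs correcting.

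The conclusion rests on linearity to week 52 and a 52-week phase. It does not establish that the slope test is underpowered, since that turns on the unreported random-slope SD. The claim that repeated measures offset the sample size is too strong rather than simply false: it holds only so far as the between-program slope variance is small.

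**What to change.** - Correct the 11-week sentence: state whether .21 is per week or per month, and the time at which d = 0.8 is meant to be reached.
- If it is per week, re-run the existing simulation with the slope that gives d = 0.8 at month 12 (about 0.045 per week) over a stated range of random-slope SDs. Report slope power as a range, separately from mean-shift power. If the 11-week horizon was deliberate, say why and give the assumed trajectory afterwards.
- Qualify the 'offsets' statement: additional weeks reduce within-program noise but not the variation in slopes between programs.

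The cost is a short re-simulation and possibly a less favourable stated figure. No additional programs are needed.

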## Discussion

HIV transmission can be effectively mitigated by identifying and engaging at-risk populations in testing and providing referrals to appropriate clinical prevention and treatment services [50]. Scaling up the delivery of these services to PWID is especially critical at a time when changes in the unregulated drug supply and associated behaviors place this historically underserved population at increased risk of infection [2–8]. SSPs, though they vary in size and scope, are uniquely poised to reach at-risk PWID, and the SAIA-SSP-HIV trial presents a novel opportunity to test the effectiveness of an organization-level implementation strategy for optimizing the delivery of HIV testing and referrals within this service setting. If successful, SAIA-SSP-HIV could be used to scale up HIV testing and service referrals among hundreds of SSPs operating across the United States, ultimately bringing the nation closer to meeting its goal of Ending the HIV Epidemic [8,51]. Findings from this trial could also inform research and programmatic efforts to scale up point-of-care testing and subsequent service referrals for other infections that cause significant morbidity and mortality among PWID such as hepatitis C, which has been prioritized for prevention efforts nationally and globally [52].

There are limitations of this study design, including a lack of individual-level outcomes (precluding, for example, analyses focused on equity in service delivery) and an exclusion of organizations that are not yet providing any HIV testing services. Distinct study designs, data collection systems, and implementation strategies could help to answer research questions about individual-level service utilization and health outcomes, or ways to best support SSPs in initiating HIV testing and referral services for the first time (which current estimates suggest comprise the minority of U.S. SSPs [30]). We also acknowledge, as another limitation, that SSPs face many challenges with service implementation that SAIA-SSP-HIV may not be able to address, including staffing and funding constraints and competing priorities of frontline staff members, leadership, and participants. However, a strength of the SAIA implementation strategy is its flexibility in tailoring goals and activities to organizations’ unique contexts through individualized coaching, which may enable organizations to achieve some service delivery improvements despite specific local constraints.

Despite these limitations, the SAIA-SSP-HIV trial, to our knowledge, represents the first RCT of an implementation strategy focused on improving an infectious disease care cascade within SSPs. It builds upon a prior pilot study suggesting the potential effectiveness of SAIA for increasing naloxone distribution through two SSPs, which resulted in a 105% average increase in the number of doses of naloxone distributed per week following initiation of the SAIA implementation strategy [28]. However, delivering HIV services in non-clinical settings like SSPs involves a distinct care cascade conceptualization, warranting additional testing through a sufficiently powered implementation trial to detect effectiveness of SAIA-SSP-HIV. Additionally, because SSPs’ operational structures vary substantially across U.S. states and local jurisdictions, this study also seeks to expand the translatability of SAIA by exploring implementation outcomes among diverse SSPs located across the country.

In conclusion, SAIA-SSP-HIV could help optimize the delivery of HIV testing and referrals in community settings that are frequented by a vulnerable, at-risk population. As the first implementation trial focused on an infectious disease care cascade within SSPs, findings from the SAIA-SSP-HIV trial will shed light on how to support non-clinical settings in optimizing delivery of screening services and subsequent referrals into clinical care. If effective, SAIA-SSP-HIV could potentially be scaled up in support of key Ending the HIV Epidemic initiatives [8,51] and could possibly be adapted for optimizing other care cascades in SSPs and other community settings.
